## 10.6 Monitoring for negative effects of treatment delivery over the internet

We will assess participant's evaluation of the internet modules and design through a feedback and rating form at the end of each module and in comments to the research assistant in emails or telephone calls.

# 11. STATISTICS

## 11.1. Description of Statistical Methods

### 11.1.1. Main Analysis

All analyses will be intent-to-treat. No interim analyses are planned. We will compare rates of PTSD and MD in each training condition using Chi square analysis. Continuous measures will be analysed using hierarchical linear modeling. This analysis models random slopes and intercepts for participants, and tests the fixed effects of repeated assessments over time (level 1) and training condition (level 2) using data from all participants. It takes into account that participants are nested within site (level 3). Variables will be centred for the analysis.

### 11.1.2. Biological Analyses

The relationship between symptom levels (PTSD and MD) and levels of salivary cortisol and C-reactive protein at post-intervention and follow-up will be analysed with hierarchical linear modelling.

### 11.1.2 Process Evaluation

A process evaluation conducted alongside the main trial will explore moderators of outcome and mediators of change. Example moderators include social support, number of traumatic events, anxiety, age, gender, years of education, neuroticism, baseline CRP and CAR, past psychiatric history, ratings of treatment helpfulness, and fidelity. Mediators of training

outcome to be considered are processes hypothesized to predict PTSD and MD in paramedics (resilience appraisals, rumination and responses to unwanted memories).

### 11.1.3 Health Economic Evaluation

A full economic evaluation will be performed to compare the costs and effects of providing iCT-R versus the placebo (already available health information). These will be performed by [name]. Data collected and the existing literature will be used in a decision analytic model to calculate the incremental costs per quality adjusted life years (QALYs) during the participant's lifetime. Uncertainty in the results will be addressed in sensitivity analyses and displayed in cost-effectiveness planes and cost-effectiveness acceptability curves.

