| Planned Trial Period               | 16 October 2017 – 30 th January 2021                                                                                                                                                                                                                                                                                                                                                                                                 |                                                                                                                                                                                                              |
|                                    | Objectives                                                                                                                                                                                                                                                                                                                                                                                                                                      | Outcome Measures                                                                                                                                                                                             |
| Primary                            | 1. Is internet-delivered cognitive training for resilience (iCT-R) more effective than accessing already available mental health information (Mind-Online) or having no specific training (standard practice), i.e., does iCT-R lead to fewer cases of PTSD and Major Depression (including subsyndromal PTSD and MD) and less PTSD and MD symptomatology at follow-up compared to Mind-Online and standard practice control conditions? | 1. Primary: Structured Clinical Interview for DSM-5 – PTSD and MD modules 

PTSD Symptom Checklist (PCL-5) 

Patient Health Questionnaire (PHQ-9)  |

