| Secondary | 
1. Does internet-delivered cognitive training for resilience (iCT-R) lead to greater improvement in secondary outcome measures (resilience, rumination, hormone and immune function, smoking, weight gain, alcohol use, symptoms of anxiety, and sleep problems, psychological distress, wellbeing) than Mind-Online and standard practice conditions?
 
2. Is iCT-R more cost-effective than Mind-Online or standard practice, i.e., is the cost per participant without an episode or symptoms of PTSD or MD and costs per QALY gained smaller?
 | 
1.
Resilience: Connor Davidson Resilience Questionnaire (CD-RISC)
Wagnild Resilience Scale
 
Rumination: Ruminative Responses Scale (RRS) (Brooding Subscale) & Responses to Intrusions Questionnaire (RIQ) dwelling subscale
 
Anxiety: Generalized Anxiety Disorder 7-item Scale (GAD-7)
 
Smoking & Alcohol Use (unpublished)
 
Weight & Height Questionnaire (unpublished)
 
Sleep problems: Insomnia Severity Index (ISI)
 
Psychological distress: General Health Questionnaire (GHQ-12)
 
Wellbeing: Warwick Edinburgh Mental Wellbeing Scale (WEMWBS)
 
Hormone function: Levels of cortisol in response to awakening and throughout the day
 
Immune function: C-reactive protein
 
2.
EuroQoL (EQ-5D-5L)
Trimbos/iMTA Questionnaire for Costs Associated with Psychiatric Illness (TiC-P)
Client Service Receipt Inventory
 |

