| participant without an episode or symptoms of PTSD or MD and costs per QALY gained smaller?                                                                                                                                                                                                                                                                                                                                                                                                                                                                                                                                                                                                                                                                                                                                                                                                                                                                                                                                                                               | Service Receipt Inventory                                                                                                                                                                                                                                                                                                                                                                                                                                                                                                                                                                                                                                                                                                                                                                                                                                                                                                                                                                                                                                                                | 2. Baseline
6 weeks
52 weeks
104 weeks                                                                                                                  |

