### 9. INTERVENTIONS

Internet-delivered cognitive training for resilience (iCT-R) and Mind-Online will be delivered over 6 weeks, with the support of the trained research assistant (wellbeing coach) by email, SMS and phone calls (on average taking up to 1 hour of research assistant time for both treatments). Participants will be able to print the modules they complete. The research assistant will send top up reminders every month and every 6 months, participants will have the opportunity to talk with the research assistant about putting their tools in place or accessing and practising the wellbeing information they have learned.

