#### 9.2 Mind-Online

The alternative resilience programme is Mind Online, a series of six modules available online covering information and advice about wellbeing and mental health topics, which have demonstrated high acceptability to emergency workers in a previous trial (4). The six modules are:

- Dealing with Stress
- Sleep Problems
- Anger
- Depression
- Post-traumatic Stress Disorder
- Mindfulness

Participants will receive the same frequency, type and duration of remote support as in iCT-R.

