### 11.2 The Number of Participants

We plan to recruit 570 participants.

The risk of student paramedics developing full syndromal PTSD and MD over two years without intervention is 10% (1), and 25% if subsyndromal PTSD and MD that cause significant distress are included. We predict that our intervention will reduce the relative risk by 50%. Setting power at 80%,  $\alpha=.05$  and hypothesizing a reduction of relative risk of 50% gives an odds ratio of 0.429, which requires a total sample size of N=304 to show a risk reduction of 50% between the active and placebo intervention. Thus, each condition would require N=152. Since we have a third condition (no-training control), the total sample size required would be N=456. Allowing for a 20% rate of attrition, we will require a total sample size of N=570.

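### The economic evaluation is planned only as iCT-R versus Mind-Online, so the standard-practice half of protocol secondary objective 2 has no planned analysis

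*Combined protocol and SAP*

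**What the plan says.** The protocol Synopsis puts secondary objective 2 as a question with two comparators: "Is iCT-R more cost-effective than Mind-Online or standard practice". The Objectives and Outcome Measures table repeats it and gives two ratios, asking whether the cost per "participant without an episode or symptoms of PTSD or MD and costs per QALY gained smaller".

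Protocol section 11.1.3 is the only description of the economic analysis. It will "compare the costs and effects of providing iCT-R versus the placebo (already available health information", using a decision model to "calculate the incremental costs per quality adjusted life years (QALYs) during the participant's lifetime". It mentions neither standard practice nor a ratio per participant free of an episode or symptoms.

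On delivery, protocol section 9 gives one figure for coach time in the two programmes, "on average taking up to 1 hour of research assistant time for both treatments". Section 9.2 adds for Mind-Online: "Participants will receive the same frequency, type and duration of remote support as in iCT-R". The SAP (Trial Design/framework) says that standard practice gets neither modules nor online support.

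The SAP (Objectives) states its secondary objectives, health economic costs included, against Mind-Online only. SAP Analysis Methods and the SAP section on Health Economics and Cost Effectiveness put the economic analysis outside the SAP. Analysis Methods adds that a plan for it will be agreed.

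**The concern.** A stated objective names two comparators and the planned analysis has one. The missing comparator is the one that bears on adoption. An ambulance education programme that does not yet offer supported online training has to decide whether to offer any, as well as which one. SAP Timing of Final Analysis speaks of early roll-out if iCT-R does better than Mind-Online or standard treatment, and the protocol Abstract hypothesises savings to the NHS and society. Both claims need a comparison with offering no programme.

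Because coach support is matched between the online arms, its cost largely cancels in the planned comparison. A favourable result against Mind-Online would not show whether supported training is worth its cost against standard practice.

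**Working it through.** **Step 1. Which arm is the placebo in 11.1.3?** The Synopsis separates the two comparators as "accessing already available mental health information (Mind-Online) or having no specific training (standard practice". Already available information is therefore Mind-Online. Section 11.2 agrees: it sizes the trial for the active against the placebo intervention and then adds an arm, "Since we have a third condition (no-training control), the total sample size required would be N=456". So 11.1.3 cannot be read as covering standard practice.

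**Step 2. Objective against analysis.**

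| Element | Protocol secondary objective 2 | Protocol 11.1.3 | SAP Objectives |
|---|---|---|---|
| Mind-Online as comparator | yes | yes | yes |
| Standard practice as comparator | yes | no | no |
| Cost per QALY | yes | yes (lifetime) | health economic costs, ratio not named here |
| Cost per participant free of an episode or symptoms | yes | no | not named |

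Elsewhere, SAP Outcome Definitions and SAP Health Economics mention only cost per QALY. Nothing in the SAP restores the missing comparator or the missing ratio.

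**Step 3. The plan's own figures.** No figure in the documents sizes the economic evaluation, but the trial's sample size supplies the risks used below. Inputs from section 11.2: risk 0.25 without intervention (subsyndromal cases included), halved to 0.125, power 80%, α = 0.05. The SAP gives two-sided testing.

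- Odds ratio = (0.125/0.875) / (0.25/0.75) = 0.429, as stated.
- With mean risk 0.1875, n per arm = [1.960 × √(2 × 0.1875 × 0.8125) + 0.842 × √(0.25 × 0.75 + 0.125 × 0.875)]² / 0.125² = (1.082 + 0.459)² / 0.015625 ≈ 152.
- 2 × 152 = 304; 3 × 152 = 456; 456 / 0.80 = 570. All match.

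The match requires Mind-Online to carry the 25% risk that section 11.2 gives for students without intervention.

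**Step 4. Size of the omitted arm.** Allocation is 1:1:1, so 570 / 3 = 190 randomised per arm. The planned comparison involves 380. After the planned 20% attrition the omitted arm is 190 × 0.80 = 152.

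**Step 5. Coach support only.** Count up to 1 hour in each online arm and 0 in standard practice.

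- iCT-R minus Mind-Online: about 0 hours.
- iCT-R minus standard practice: up to 1 hour.

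The documents give no unit cost, so the hourly rates here are assumptions. The risk difference against standard practice is taken as 0.25 − 0.125 = 0.125. Support cost per case avoided = hourly rate / 0.125.

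| Assumed rate per hour | Added support cost vs Mind-Online | Added support cost vs standard practice | Support cost per case avoided vs standard practice |
|---|---|---|---|
| £15 | about £0 | up to £15 | up to £120 |
| £30 | about £0 | up to £30 | up to £240 |
| £60 | about £0 | up to £60 | up to £480 |

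These amounts show only where the support cost appears. They are not estimates of cost-effectiveness.

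**Step 6. Are the data there?** Appendix B schedules the EQ-5D-5L, TiC-P and CSRI at baseline, 6, 52 and 104 weeks with no restriction by arm. Section 9.4 offers iCT-R to standard-practice participants only at 104 weeks, so the randomised comparison is intact to that point.

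**The case against.** The strongest reply is that 11.1.3 is an outline and the comparators can still be settled in the economic plan that the SAP says will be agreed. The planned comparison also matches the SAP's own objective, and Mind-Online is a legitimate comparator that the protocol objective names first. Much of this stands. It makes the gap cheap to close and shows that the protocol and SAP objectives must be reconciled. It does not remove the gap: the only texts on comparators that the pending plan would inherit are 11.1.3 and the SAP objective, and both leave out standard practice.

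A reader might infer three stronger things that the documents do not support.

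- *That the evaluation cannot answer its objective at all.* It answers the Mind-Online half.
- *That the two programmes cost about the same, so almost any QALY gain would look cost-effective.* Only coach support is matched, and the 1 hour is a ceiling on an average. No hosting, licence, production or unit cost is given. iCT-R has purpose-made video and audio, whereas Mind-Online is already online. Service use and productivity costs, measured by the CSRI and TiC-P, may also differ by arm.
- *That the standard-practice data will go unused.* Section 11.1.3 feeds collected data and literature into a model and does not exclude that arm as an input. What is missing is a stated comparison.

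**Conclusion.** The point holds as a mismatch between a stated secondary objective and its planned analysis. One of two named comparators, and one of two named ratios, has no analysis in either document. The omitted arm is about 190 of the 570 randomised participants (152 after planned attrition). The difference in coach support, up to 1 hour per participant on average, appears only in the omitted comparison.

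The textual finding rests on no assumption. The cost illustration rests on the assumed hourly rates, on the plan's 25% and 12.5% risks, and on counting coach support alone. On those same premises Mind-Online would cost more than standard practice with no gain, which is a reason not to let it be the only reference. That step is conditional and could change once other costs are counted.

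This is a secondary objective whose detailed plan is still open. It should be corrected before that plan is agreed, and it does not affect the primary analysis.

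**What to change.** 1. Amend protocol section 11.1.3 to an incremental analysis of all three randomised arms (standard practice, Mind-Online, iCT-R), with cost-effectiveness acceptability curves covering all three.
2. Replace the word placebo in 11.1.3 with the arm's name.
3. Reconcile the protocol's secondary objective 2 with the SAP Objectives, so that both name the same comparators.
4. Report both ratios in the objective: cost per QALY, and cost per participant free of an episode or symptoms.
5. Write all of this into the pending health-economic plan before the economic data are analysed. Details such as ranking by cost, removal of dominated options and the source of programme costs belong there.

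The cost is some wording and a little more modelling. No new data are needed from participants, because the EQ-5D-5L, TiC-P and CSRI are already scheduled without restriction by arm. The sample size does not change.

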### 11.2 The Number of Participants

We plan to recruit 570 participants.

The risk of student paramedics developing full syndromal PTSD and MD over two years without intervention is 10% (1), and 25% if subsyndromal PTSD and MD that cause significant distress are included. We predict that our intervention will reduce the relative risk by 50%. Setting power at 80%,  $\alpha=.05$  and hypothesizing a reduction of relative risk of 50% gives an odds ratio of 0.429, which requires a total sample size of N=304 to show a risk reduction of 50% between the active and placebo intervention. Thus, each condition would require N=152. Since we have a third condition (no-training control), the total sample size required would be N=456. Allowing for a 20% rate of attrition, we will require a total sample size of N=570.

### 11.3 The Level of Statistical Significance

Significance levels were set at  $p < .05$ .

### 11.4 Criteria for the Termination of the Trial

There are no stopping rules for the trial as it is a low risk non-CTIMP.

### 11.5 Inclusion in Analysis

Analyses will be intent-to-treat, i.e. all randomized participants will be included in the analysis.

## 12. DATA MANAGEMENT

### 12.1. Source Data

Source data will be captured online via Qualtrics software. Access to the system will be restricted to named study personnel only and via password protection. We have arranged with the University of Oxford IT services for the files to be encrypted and backed up on a weekly basis using the Tivoli Storage Manager, the data are copied to three separate tapes. One copy resides in the Tape Robot in the IT Services Machine room. The other two copies are held in locked fireproof safes, one onsite at IT Services, one offsite in locked premises. The data on the tapes are inaccessible without the TSM database. The data on the offsite tapes are encrypted.

## 12.2. Access to Data

Direct access will be granted to authorised representatives from the host institution and the regulatory authorities to permit trial-related monitoring, audits and inspections.

## 13. QUALITY ASSURANCE PROCEDURES

The trial will be conducted in accordance with the current approved protocol, relevant regulations and standard operating procedures. Regular monitoring will be performed. Data will be evaluated for compliance with the protocol, and completeness and accuracy in relation to source documents (e.g., for SCID-5). The trial steering committee will regularly view recruitment rates, compliance with delivery of different training programmes and completeness of data collection.

## 14. ETHICAL AND REGULATORY CONSIDERATIONS

### 14.1. Declaration of Helsinki

The Investigator will ensure that this trial is conducted in accordance with the principles of the Declaration of Helsinki.

### 14.2. Guidelines for Good Clinical Practice

The Investigator will ensure that this trial is conducted in accordance with relevant regulations and with Good Clinical Practice.

### 14.3. Approvals

The protocol, informed consent form, participant information sheet and advertising material has been submitted and approved by the University of Oxford Inter-Divisional Medical Sciences Research Ethics Committee (REC).

#### 14.4. Participant Confidentiality

The trial staff will ensure that the participants' anonymity is maintained. The participants will be identified only by a participant ID number on all trial documents and any electronic database, with the exception of the signed consent form, where participant initials may be added. All documents will be stored securely and only accessible by trial staff and authorised personnel. The trial will comply with the Data Protection Act, which requires data to be anonymised as soon as it is practical to do so.

#### 14.6. Expenses and Benefits

Participants will be paid 30 pounds for their time at 104 weeks.

### 15. FINANCE AND INSURANCE

#### 15.1. Funding

The trial is funded by MQ, awarded to [name] and [name].

#### 15.2. Insurance

The University has a specialist insurance policy in place which would operate in the event of any participant suffering harm as a result of their involvement in the research (Newline Underwriting Management Ltd, at Lloyd's of London).

### 16. PUBLICATION POLICY

The results of the trial will be published in peer-reviewed international journals and will be made open access.

## 15. Trial Flow Chart

[figure not shown]

659 APPENDIX B: SCHEDULE OF PROCEDURES  
660

| Procedures                                             | Assessments |         |          |          |           |
|--------------------------------------------------------|-------------|---------|----------|----------|-----------|
|                                                        | Baseline    | 6-weeks | 24-weeks | 52-weeks | 104-weeks |
| Informed consent                                | X           |         |          |          |           |
| Screening                                       |             |         |          |          |           |
| PHQ-9                                                  | X           | X       | X        | X        | X         |
| PCL-5                                                  | X           | X       | X        | X        | X         |
| Randomisation                                   | X           |         |          |          |           |
| Interviews                                      |             |         |          |          |           |
| Structured Clinical Interview DSM-5: PTSD & MD modules | X           | X       |          | X        | X         |
| Questionnaires                                  |             |         |          |          |           |
| CD-RISC                                                | X           | X       |          | X        | X         |
| Wagnild                                                | X           | X       |          | X        | X         |
| GAD-7                                                  | X           | X       |          | X        | X         |
| Smoking & Alcohol                                      | X           | X       |          | X        | X         |
| Weight                                                 | X           | X       |          | X        | X         |
| ISI                                                    | X           | X       |          | X        | X         |
| GHQ                                                    | X           | X       |          | X        | X         |
| WEMWBS                                                 | X           | X       |          | X        | X         |
| EQ5D5L                                                 | X           | X       |          | X        | X         |
| Trimbos/iMTA-TiC-P                                     | X           | X       |          | X        | X         |
| CSRI                                                   | X           | X       |          | X        | X         |
| EPQ                                                    | X           |         |          | X        | X         |
| SS                                                     | X           | X       |          | X        | X         |
| RRS (Brooding)                                         | X           | X       |          | X        | X         |
| RIQ                                                    | X           | X       |          | X        | X         |
| TS                                                     | X           | X       | X        | X        | X         |
| Duration, Frequency, Distress linked to intrusions     | X           | X       | X        | X        | X         |
| Concrete & Abstract Thinking                           | X           | X       | X        |          |           |
| Biological samples                              |             |         |          |          |           |
| Cortisol                                               | X           | X       |          | X        | X         |
| CRP                                                    | X           | X       |          | X        | X         |
| Compliance                                      |             |         |          |          |           |
| Practice iCT-R/Mind-Online tools                       |             | X       | X        | X        | X         |

661  
662

